### Strategies to improve adherence to interventions

LOS is our primary outcome, and we recognize it can be easily manipulated, therefore we planned to take every possible precaution to limit bias. Post-operatively, patients will remain blinded to the intervention with the use of opaque bandages as if a midline incision and six robotic port sites were made (Fig. 1). As an additional precaution an abdominal binder will be placed on all patients and left in place for the duration of hospital stay. Patients will be discharged by a blinded assessor who is a fellowship trained hernia surgeon, but not an enrolling surgeon in the trial. On postoperative day 1, both the patient and the blinded assessor surgeon will be asked to postulate if the surgery was robotic or open. Discharge criteria was established to standardize the two groups, which consist of the following: tolerating oral diet, ambulating, and pain is controlled with oral medications. The operating surgeon will continue to care for the patient post-operatively but cannot be the surgeon ordering the discharge. If drains are present, they will remain at the discretion of the operating surgeon. If the patient is discharged with drains, these will be removed later in the outpatient setting at the direction of the operating surgeon.

**Fig. 1 Fig1:**
[figure not shown]
Dressing diagram. Every patient receives 6 island and 1 midline Primapore dressing, regardless of surgery performed

### Outcomes

Primary outcome: Hospital Length of stay (hours).

Secondary Outcomes:Patient Reported Outcomes at baseline, 30 (± 14 days), 1-year (± 90) days and 2-year follow-upoHerQLes summary scoreoShort-form Patient-Reported Outcomes Measure Information System (PROMIS) Pain Intensity Scale[11] scoreoEuraHSoNRS 11 (also scored the 5 following days after surgery)Opioid consumptionHernia recurrenceAll complications during hospitalization, 30 days, 1-year follow-up postoperatively.Wound morbidityoSSIoSSOoSSOPIReadmissionPerform a formal cost effectiveness analysis utilizing quality adjusted life years and incremental cost effectiveness ratios.

### Participant timeline

Estimated patient accrual time is 3–4 years. Data collection will occur over 3 years from randomization of each patient and includes baseline, hospital stay, 30 days, 1-year days follow ups. Details are shown in the Table 1.

**Table 1 Tab1:** Schedule of enrollment, interventions and assessments

	Baseline	Hospital-stay	30-day	1-Year
Documentation of Inclusion/Exclusion	X			
Informed Consent	X			
Randomization	X			
NRS-1	X	X	X	X
PROMIS 3a SF	X		X	X
HerQLes	X		X	X
Opioid Consumption	X	X	X	X
EuraHS	X		X	X
Direct costs		X		
Composite recurrence				X
Hernia recurrence inventory				X

Scheduled Interventions applied to consented patients during baseline, hospital stay, 30 day and one year follow-up

### Sample size

Using an alpha of 0.05, a power of 0.90, and determining a 24-h difference in length of stay, the necessary sample size is 86 patients in each arm, yielding a total of 172 patients. Estimating 10% attrition at 30 days, 200 patients would be needed, 100 patients enrolled in each arm.

### Recruitment

This is a multi-center trial from selected high volume hernia centers with fellowship trained hernia experts. Recruitment will take place at Cleveland Clinic, University of Tennessee, Prisma Health, and University of Florida. We expect to complete enrollment within 3–4 years.

## Assignment of interventions: allocation

### Sequence generation

Patients will be randomized in a 1:1 ratio using a computer-generated permuted block method with random block sizes. Computer-generated treatment random allocation in REDCap® will randomize robotic or open retromuscular hernia repair in the clinic office after consenting. However, since the scheduling requires prior knowledge of how the surgery will be performed (open or robotic), the operating surgeon will know the randomization arm.

### Concealment mechanism

The randomization table was generated by a statistician and concealed from the study team within REDCap®

### Implementation

Patients will be enrolled during preoperative consultation in the outpatient setting. The allocation sequence will be generated by the research coordinator in REDCap®.

## Assignment of interventions: Blinding

### Who will be blinded

Study participants and the assessor for discharge will be blinded. Additionally, operative notes are blinded to the assessing discharge surgeon. Peri-operative nursing and anesthesia have been educated and precautions taken to decrease the possibility of the patient being unblinded unintentionally. These include direct communication to the anesthesia staff and perioperative nursing the day of surgery. Pre- and post-operatively, a sign is placed in the patient chart and over the bed to inform all caregivers that the patient is in a trial where they cannot be informed of the operative approach.

### Procedure for unblinding if needed

Participants will be unblinded after 6 months, if they inquire about the randomization arm.

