### Trial design

This is a multi-center, registry-embedded, double-blinded, randomized controlled trial. Study data will be captured in the Abdominal Core Health Quality Collaborative (ACHQC) registry and supplemented with Research Electronic Data Capture (REDCap®) for variables outside of the ACHQC. These include LOS measured in hours, operating time, direct cost, NRS 11 pain scores, and EuraHS scores.

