### Data collection and management

#### Plans for assessment and collection of outcomes

HerQLes, a validated 12 question survey with an MCID of 15.6, will be collected at baseline and each time point to assess abdominal wall-specific quality of life [12, 13]. PROMIS 3a Pain Intensity Surveys will be collected at all timepoints to assess pain [11]. EQ-5D-5L with visual assessment score will be collected at all timepoints to assess overall quality of life [14]. Hernia recurrence will be measured using a pragmatic definition [15]. Cross sectional imaging will be assessed by three surgeons blinded to the operating surgeon and randomization with recurrence defined by consensus of at least two. In the absence of imaging, a clinical exam will be used to assess recurrence. In the absence of either imaging or clinical exam, the patient response to the presence of a bulge on the Hernia Recurrence Inventory [16]. Patients will also be asked to guess their intervention allocation at 1 year postoperatively.

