#### Plans to promote participant retention and complete follow-up

Patients are scheduled for standard of care clinic appointments at 30 days and 1 year and 5 years postoperatively. Patients will be contacted by the research team for patient reported outcomes in the 2-year follow-up window and scheduled for a CT and clinical visit if they report a bulge on the HRI, which is considered standard of care. We will promote complete follow up through multiple approaches. The 30-day follow-up period will extend from 16 to 44 days postoperatively, the 1-year follow-up period will extend from 9 to 15 months postoperatively, the 2-year follow-up period will extend from 18 to 30 months postoperatively, and the 5-year follow-up period will extend from 54 to 66 months postoperatively. Appointment reminders will be sent via patient online portals and nursing phone calls. Virtual follow-up visits can be accommodated, and patients can complete imaging at their local institutions. For patients who have missed follow-up appointments, the dedicated study coordinator, research fellow, and/or surgeon will call patients to reschedule and/or collect patient reported outcomes over the phone. This will increase convenience for patients and protocol adherence. Appropriate statistical analyses will be conducted to account for missing data.

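### On-request disclosure of the arm from 6 months comes before the 1-year self-reported outcomes and the 1-year allocation guess

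*Protocol article*

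**What the plan says.** The Trial design section describes the study in these words: "This is a multi-center, registry-embedded, double-blinded, randomized controlled trial". Under Who will be blinded the article states: "Study participants and the assessor for discharge will be blinded". That section gives no date on which participant blinding ends. The next section, Procedure for unblinding if needed, supplies one: "Participants will be unblinded after 6 months, if they inquire about the randomization arm". It does not require any assessment to be complete first.

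The section on retention and follow-up fixes the windows. The early visit may fall anywhere between days 16 and 44. For the next visit the wording is: "the 1-year follow-up period will extend from 9 to 15 months postoperatively". The window at 2 years covers months 18 to 30. Table 1 places the numeric pain score, PROMIS 3a, HerQLes, EuraHS and the Hernia Recurrence Inventory at 1 year. The Outcomes section adds patient-reported outcomes at 2 years. Secondary analyses names 30 days and 1 year as the times at which the arms are compared on the four self-reported scores.

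The section on assessment and collection of outcomes sets a hierarchy for recurrence: imaging read by blinded surgeons, then clinical examination, and only when both are lacking "the patient response to the presence of a bulge on the Hernia Recurrence Inventory". It then adds: "Patients will also be asked to guess their intervention allocation at 1 year postoperatively". A separate guess, by the patient and the discharge assessor, is taken on postoperative day 1 (Strategies to improve adherence to interventions).

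**The concern.** Two stated rules do not fit together. Patients may be told their arm on request from 6 months, and the same patients are asked at 1 year to guess it. This is more than operational detail left to a fuller document, because the disclosure rule undercuts an assessment that the article itself schedules.

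The 1-year pain and quality-of-life scores are the patient's own report. A patient who knows which approach was used may answer differently. Those who ask select themselves, and they may differ between arms in number or in kind. One of the two time points named for the self-reported comparisons therefore comes after the date from which blinding may be lifted. The 1-year guess, pooled over all patients, would mix two things: how well concealment worked, and how many patients were told.

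**Working it through.** **Order of events.** The inputs are the disclosure rule and the follow-up windows quoted above. The article does not say from what date the 6 months run; surgery is assumed here. Randomization happens earlier, in clinic, so counting from it would only lengthen the gap.

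| Assessment | When | Relative to 6 months |
|---|---|---|
| Length of stay | ends at the discharge order | before |
| Day-1 guess | postoperative day 1 | before |
| Daily pain scores | first 5 days after surgery | before |
| 30-day outcomes | 16 to 44 days | before |
| 1-year scores, recurrence inventory, allocation guess | 9 to 15 months | 9 − 6 = 3 to 15 − 6 = 9 months after |
| 2-year patient-reported outcomes | 18 to 30 months | 18 − 6 = 12 to 30 − 6 = 24 months after |

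**Effect on the pooled guess.** Let *f* be the share told by the time of the guess. The article does not give it, so a range is assumed. Suppose that everyone told answers correctly and everyone else guesses at random, which means that blinding is perfect apart from disclosure. The correct-guess rate is then *f* + (1 − *f*)/2. The last column is the normal-approximation probability that a two-sided 0.05 test rejects 50%. It uses N = 172, the article's sample size before allowance for attrition.

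| *f* (assumed) | Correct guesses | Probability of rejecting 50% |
|---|---|---|
| 5% | 0.05 + 0.475 = 52.5% | about 10% |
| 10% | 0.10 + 0.45 = 55% | about 26% |
| 20% | 0.20 + 0.40 = 60% | about 75% |
| 30% | 0.30 + 0.35 = 65% | about 98% |
| 50% | 0.50 + 0.25 = 75% | about 100% |

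Under the same assumption, the guess among patients not told stays at 50%. The contamination comes from pooling and does not spoil every answer.

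**Effect on a self-reported mean.** If a share *f* in each arm is told, and knowing the arm changes the between-arm difference among those told by *b* points, the overall contrast moves by *f* × *b*. Neither quantity is in the article. With an assumed *f* of 20% to 50% and *b* of 3 to 8 HerQLes points, the movement is 0.20 × 3 = 0.6 to 0.50 × 8 = 4.0 points. Against the stated minimal clinically important difference of 15.6, that is 0.6/15.6 = 4% to 4.0/15.6 = 26%. If knowing the arm shifted both arms equally, *b* would be zero and the contrast would not move.

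**Recurrence.** The patient's bulge answer decides the outcome only when there is neither imaging nor examination. It has a second role at 2 years, when a reported bulge leads to CT and a clinic visit, so patient report then influences who is imaged.

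**The case against.** The strongest defence is that blinding here serves the primary outcome. The article introduces the dressings, the binder and the blinded discharge surgeon as safeguards for length of stay, and that outcome is complete at the discharge order. The day-1 guess is the check that matches it, and disclosure at 6 months touches neither. This stands, and it confines the point to later secondary outcomes.

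Several stronger readings are tempting, and the article does not support them:

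- **That the 1-year outcomes are biased.** Disclosure depends on asking, and nothing is said about how many ask or how knowing affects answers. The text supports only that they can be biased.
- **That the 1-year guess is meaningless.** It is invalid for patients already told, but it can still be read among those not told, provided that disclosures are recorded. The full protocol may already provide for recording.
- **That recurrence is broadly compromised.** Imaging readers are blinded to randomization, a 1-year clinic visit is scheduled as standard of care, and the bulge item is the last resort.

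It can also be said that patients may work out their arm once the dressings are off, so that delaying disclosure gains little. The article gives no information on this. If true, it would shrink the added bias, but it would not explain why a guess is scheduled after permitted disclosure.

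A last objection concerns remedies. Dropping patients who were told excludes them on self-selected behaviour after randomization, and departs from the intention-to-treat basis. That is correct, and such an analysis can only be supportive.

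**Conclusion.** The point holds for timing and is modest in consequence. The disclosure rule precedes every 1-year and 2-year patient-reported outcome, the recurrence inventory and the 1-year guess. It can bias the 1-year self-reported comparisons, and it contaminates the pooled guess.

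The timing rests on the article's own windows and on counting 6 months from surgery. Every figure for size rests on assumed shares and shifts. Under those assumptions a HerQLes contrast moves by 0.6 to 4.0 points, well below the stated 15.6. The guess is more sensitive: with 20% told, a test against 50% would reject about three times in four although blinding was otherwise intact. The primary analysis and the sample size are not affected. This is a worthwhile, inexpensive correction to secondary outcomes.

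**What to change.** 1. Amend Procedure for unblinding if needed so that disclosure on request takes place only once the patient's 1-year assessment is complete or the 15-month window has closed, except for medical need.
2. Ask the late allocation guess before any disclosure is possible, for example at the 30-day visit. Otherwise, restrict the 1-year guess to patients who have not been told.
3. Record the date of every disclosure.
4. Keep the intention-to-treat comparison of the 1-year scores as the main analysis. Label any analysis that sets aside patients told earlier as supportive only, because those patients are self-selected.
5. State in the report that the 2-year outcomes were collected after disclosure was permitted. The change in item 1 covers both comparison times named in Secondary analyses, but not 2 years.

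The cost is a short amendment and an instruction to coordinators. Patients who ask would wait up to about 15 − 6 = 9 months longer. Recruitment began in July 2022, so patients already past 6 months may have been told under the existing rule. The amendment cannot undo that, and the trial would contain patients handled under both rules. For those already told, the disclosure dates and the supportive analysis are what remain.

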### Data collection and management

#### Plans for assessment and collection of outcomes

HerQLes, a validated 12 question survey with an MCID of 15.6, will be collected at baseline and each time point to assess abdominal wall-specific quality of life [12, 13]. PROMIS 3a Pain Intensity Surveys will be collected at all timepoints to assess pain [11]. EQ-5D-5L with visual assessment score will be collected at all timepoints to assess overall quality of life [14]. Hernia recurrence will be measured using a pragmatic definition [15]. Cross sectional imaging will be assessed by three surgeons blinded to the operating surgeon and randomization with recurrence defined by consensus of at least two. In the absence of imaging, a clinical exam will be used to assess recurrence. In the absence of either imaging or clinical exam, the patient response to the presence of a bulge on the Hernia Recurrence Inventory [16]. Patients will also be asked to guess their intervention allocation at 1 year postoperatively.

#### Plans to promote participant retention and complete follow-up

Patients are scheduled for standard of care clinic appointments at 30 days and 1 year and 5 years postoperatively. Patients will be contacted by the research team for patient reported outcomes in the 2-year follow-up window and scheduled for a CT and clinical visit if they report a bulge on the HRI, which is considered standard of care. We will promote complete follow up through multiple approaches. The 30-day follow-up period will extend from 16 to 44 days postoperatively, the 1-year follow-up period will extend from 9 to 15 months postoperatively, the 2-year follow-up period will extend from 18 to 30 months postoperatively, and the 5-year follow-up period will extend from 54 to 66 months postoperatively. Appointment reminders will be sent via patient online portals and nursing phone calls. Virtual follow-up visits can be accommodated, and patients can complete imaging at their local institutions. For patients who have missed follow-up appointments, the dedicated study coordinator, research fellow, and/or surgeon will call patients to reschedule and/or collect patient reported outcomes over the phone. This will increase convenience for patients and protocol adherence. Appropriate statistical analyses will be conducted to account for missing data.

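### An arm-aware surgeon is not excluded from collecting patient-reported outcomes by phone after missed visits, which could bias secondary outcomes and unblind patients at 30 days

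*Protocol article*

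**What the plan says.** All references are to the protocol article.

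- **Plans to promote participant retention and complete follow-up.** When a visit is missed, the study coordinator, "research fellow, and/or surgeon will call patients to reschedule and/or collect patient reported outcomes over the phone". Nothing is said about whether the caller knows the arm.
- **Sequence generation.** Because the operation has to be scheduled, "the operating surgeon will know the randomization arm".
- **Strategies to improve adherence to interventions.** "The operating surgeon will continue to care for the patient post-operatively but cannot be the surgeon ordering the discharge".
- **Who will be blinded.** "Study participants and the assessor for discharge will be blinded". People who collect patient-reported outcomes are not mentioned.
- **Procedure for unblinding if needed.** "Participants will be unblinded after 6 months, if they inquire about the randomization arm".
- **Plans for assessment and collection of outcomes.** Recurrence is assessed in tiers. For the first tier, "Cross sectional imaging will be assessed by three surgeons blinded to the operating surgeon and randomization". Clinical examination comes next. The last tier is: "In the absence of either imaging or clinical exam, the patient response to the presence of a bulge on the Hernia Recurrence Inventory". That sentence has no verb, but its place in the sequence shows that the answer then decides. The same section adds: "Patients will also be asked to guess their intervention allocation at 1 year postoperatively".

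**The concern.** The trial is described as double-blinded, and pain, HerQLes, PROMIS, EuraHS and the bulge item are all subjective. The retention section permits a person who may know the arm to elicit these answers in conversation, in patients whose data would otherwise be missing. Where the protocol wants a surgeon kept away from an outcome, it says so: the discharge assessor may not be an enrolling surgeon, and the image readers are blinded. The phone call carries no such limit.

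Three things are at stake:

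1. **Secondary scores.** The comparisons at 30 days and 1 year could shift if surgeons call more often in one arm, or influence answers more in one arm.
2. **Recurrence.** A patient reached only by phone is likely to have neither imaging nor examination, so the least protected tier of the definition applies.
3. **Patient blinding.** A call around 30 days from someone who knows the arm could disclose it. That would also contaminate the 1-year allocation guess.

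**Working it through.** The plan states no figure on this point, so there is nothing to reproduce. The check is a comparison of sections, followed by an illustration of scale.

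**Step 1. Is an arm-aware caller permitted?** The retention section names a surgeon without qualification. The operating surgeon knows the arm, stays involved after surgery, and is barred only from ordering discharge. No section blinds those who collect outcomes. So the text permits it, though it does not say that the calling surgeon is the operating surgeon.

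**Step 2. Are other callers arm-aware?** Possibly. The Implementation section gives the research coordinator a role in allocation within REDCap, and the Data management section keeps allocation and quality-of-life scores in REDCap. The concern therefore does not stop at the surgeon.

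**Step 3. Is the patient still meant to be blinded at the time of the call?** The 30-day window is days 16 to 44, which lies wholly before 6 months. The 1-year window (9 to 15 months) and the 2-year window (18 to 30 months) lie after it. The unblinding risk therefore belongs mainly to the 30-day window.

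**Step 4. Does the call reach the recurrence outcome?** The sentence on calls names patient-reported outcomes in general, not the Hernia Recurrence Inventory. The inventory is answered by the patient, so taking it in the same call is a reasonable inference, but it remains one.

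**Step 5. Does the call reach the primary endpoint?** No. Length of stay ends at the discharge order, before any follow-up call.

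**Step 6. Scale.** Let f be the share of patients in each arm scored by an arm-aware caller, and s the shift that this causes.

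Bias in the mean difference = f(robotic) × s(robotic) − f(open) × s(open)

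With equal shares this is f × b, where b is the difference in shift between arms. If shares and shifts are equal, b = 0 and the bias is 0. The protocol gives neither f nor b. Its assumed 10% attrition at 30 days is only a rough anchor for f, and the HerQLes MCID of 15.6 serves only to scale b. Assumed values give, in HerQLes points:

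| f | b = 5 | b = 10 | b = 15.6 |
|---|---|---|---|
| 5% | 0.25 | 0.50 | 0.78 |
| 10% | 0.50 | 1.00 | 1.56 |
| 20% | 1.00 | 2.00 | 3.12 |
| 40% | 2.00 | 4.00 | 6.24 |

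Unequal call rates alone also suffice. A 5-point shift in both arms, with 20% called in one arm and 10% in the other, gives 0.20 × 5 − 0.10 × 5 = 0.5 points.

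For recurrence, let d be an assumed difference between arms in the probability of reporting a bulge, caused by the caller, and let f now be the share classified by the bulge answer in such a call. With d of 10 to 20 percentage points, f × d is 1 to 2 points at f = 10% and 4 to 8 points at f = 40%.

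**The case against.** The case on the other side is substantial.

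- **The text says surgeon, not operating surgeon.** A reader might infer that the unblinded operating surgeon will make these calls. The documents do not say so: the surgeon is listed last of three callers, and non-enrolling hernia surgeons also work in the trial. What stands is that the operating surgeon is not excluded and is the natural person to call as the continuing carer.
- **A reader might infer that the scores are biased.** The documents support only that they could be. An influence that is equal in both arms, at equal call rates, cancels.
- **The blinding measures mainly protect length of stay.** The article ties the dressings and the binder to that outcome, and the binder stays on only in hospital. It would be too strong to say that the calls undo the trial's blinding. Still, participants are meant to stay blinded up to 6 months, which covers the 30-day calls.
- **The surgeon already sees the patient.** A call is not the only route to disclosure, and nothing shows that scores at scheduled visits are collected away from the surgeon. This is fair. It limits how much risk the call adds, but does not justify the permission.
- **A reported bulge at 2 years leads to a CT and a clinic visit, with blinded reading.** This protects against a false positive answer. The trigger is written for the 2-year window only, whereas Table 1 schedules the inventory at 1 year. A false negative answer would escape it in any case.
- **An article leaves caller scripts to the full protocol.** That is true of scripts. Here, however, the article states who may collect the answers, so the point concerns a stated permission and not an omission.

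**Conclusion.** The point holds in a limited form. The article permits a surgeon to collect subjective outcomes by phone after a missed visit, without excluding the operating surgeon who knows the arm. This could bias the secondary patient-reported scores, and recurrence where the bulge answer decides, if surgeon calls or their influence differ between arms. A 30-day call could unblind a patient before 6 months; at 1 and 2 years this matters less, because patients may already have asked and been told. Length of stay is untouched.

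The size cannot be derived from the document. The figures above rest on assumed shares and shifts, and the larger ones are extremes. At a 10% share, even a difference in shift as large as the MCID moves the HerQLes comparison by 1.56 points, one tenth of the MCID. The change is worth making because it is cheap and closes a gap in a trial presented as double-blinded, not because a large bias has been shown.

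**What to change.** In the retention section:

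1. Limit the operating surgeon's call to rescheduling.
2. Have patient-reported outcomes and the Hernia Recurrence Inventory self-completed by portal or mail where possible. Otherwise, have them read verbatim from a script by one of the staff already named who took no part in the operation and, where feasible, does not know the allocation. The coordinator who handles allocation may know it, so naming existing staff is not enough by itself.
3. Record the mode of collection and the caller's role for each response in REDCap.
4. Add a sensitivity analysis that excludes answers collected by arm-aware callers. The planned mixed models can keep these patients with the score missing. For recurrence, show the number classified by such answers in each arm.

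**Cost.** Revised wording, a short script, two REDCap fields and one extra analysis. Full caller blinding would also need separated roles or restricted access to allocation, which is why it is asked for only where feasible. Slightly fewer responses may be recovered.

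**Timing.** Recruitment was expected to end in July 2025. Counting from then, the 1-year window closes 15 months later, in October 2026, and the 2-year window 30 months later, in January 2028. For late enrolments the change mainly protects the later scores and recurrence; answers already collected need the caller recorded retrospectively where it is known.
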